### Objectives

This paper describes the protocol for a randomized controlled trial for the mental illness; supportive, preventative, online, targeted (mi.spot) intervention. It is hypothesized that following the mi.spot intervention, young adults will report the following:

Significant improvements in mental health and well-being (primary outcomes)Significant improvements in coping, social connectedness, and attribution of responsibility for parental mental illness (secondary outcomes)Significant increases in help seeking and mental health literacy (secondary outcomes).

Furthermore, the study will determine what components of the site participants use and do not use, along with their views about intervention safety and acceptability. Facilitators’ views of the feasibility of the intervention will also be sought.

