### Primary Outcome Measures

The primary outcome measures used in this study are as follows:

The Mental Health Continuum short form is an internationally applied and thoroughly validated self-administered rating scale that contains items that measure 3 aspects of well-being: emotional, social, and psychological. Participants are asked the degree to which they have experienced emotional, social, and psychological well-being over the past month. The form includes a 6-point Likert scale from 0=never to 5 every day. Scores on this scale can range from 0 to 70, and higher scores indicate higher levels of well-being [23].The *Depression, Anxiety, and Stress Scale* is an internationally applied and thoroughly validated self-administered rating scale that measures levels of depression, anxiety, and stress. Participants are asked the degree to which they have experienced depression, anxiety, and stress over the past month. A 4-point Likert scale is used from 0 (did not apply to me at all) to 3 (applied to me very much or most of the time) within each of the 3 domains. Normal scores for depression, anxiety, and stress ranged from 0 to 4, 0 to 3, and 0 to 7, respectively, and scores above these ranges indicate mild to extremely severe levels in each domain [24,25].

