### Participant Numbers

A total of 70 18- to 25-year-olds will be recruited. Participant numbers were initially determined by a power calculation indicating that a minimum of 44 participants, with Crit F=3.10 (using GPOWER 3.1, assuming 2 groups and 3 repetitions, a small effect size, an alpha of 5%, and power of 95%), will be required. However, based on previous dropout rates (the pilot study), it was considered that over the time frame of data collection (including the longer frame of the wait-list controls), there may be a dropout rate of up to 40%. As a consequence, recruitment numbers were increased to 70.

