## Results

### Data Analysis

The impact of mi.spot on participants will be examined at pre, post, and follow-up time periods using analyses of variance on each of the measures outlined above. There will be a within-subjects factor (time) and a between-subjects factor (intervention/control). Data analysis will employ the intention-to-treat principle by including all participants in the analyses.

Interview data will be analyzed within a qualitative framework using interpretative phenomenological analysis (IPA). IPA is an approach that examines participants’ experiences and meanings of a phenomenon [34], and in this case, the facilitator’s and participants’ experiences of mi.spot. IPA also provides a structure for coding and categorization of data [34] and will be used to develop responses to questions regarding feasibility and acceptability. Before analysis, respondent validation will occur, a process that entails providing participants with a copy of their transcript and an invitation to delete any information they believe may be identifiable and/or modify existing or add any information. A second researcher will independently analyze one third of all transcripts. Rather than a numerical index of agreement, consensus will be reached by discussion and referring back to participants’ transcripts.

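### Two to four primary scores each get their own ANOVA, but the only stated alpha is an unadjusted 5% for a single test, and nothing says which results make a primary success

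*Protocol article*

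**What the plan says.** The Objectives section lists "Significant improvements in mental health and well-being (primary outcomes") as its first hypothesis, with the outcomes in the plural. Primary Outcome Measures then gives two instruments. The Mental Health Continuum short form has one total, from 0 to 70. The DASS is rated "within each of the 3 domains" (depression, anxiety, stress), each with its own normal range, and no DASS total is described.

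Data Analysis plans to proceed "using analyses of variance on each of the measures outlined above", with time as the within-subjects factor and group as the between-subjects factor. It ranks no primary outcome above another and does not say how the primary results combine.

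Alpha appears only under Participant Numbers. That section reports "a minimum of 44 participants, with Crit F=3.10", for 2 groups and 3 repetitions, "a small effect size", "an alpha of 5%, and power of 95" per cent. It gives no numerical effect size and no correlation among the repeated measures.

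**The concern.** A design sized for one test at 5% is paired with a primary objective that is tested two or more times. With no rule joining the results, the choice of which significant scale represents the primary finding can be made after the data are seen. One significant score out of several could then be reported as a primary effect, with a false-positive risk above the 5% in the sample-size paragraph. The article promises reliable evidence and plans dissemination to practitioners and policy makers, so how the main claim is controlled matters.

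**Working it through.** **Inputs from the article.** Alpha 5%, power 95%, 2 groups, 3 time points, N = 44, critical F = 3.10, dropout up to 40%, 70 recruited. Primary scores: two measures at least, four if the DASS domains are tested separately.

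**Inputs assumed.** Common correlation r between primary outcomes, taken from 0 to 0.8. Effect size f and correlation rho among repeated measures, inferred from the stated N. Sphericity. The group-by-time interaction as the test of interest: the article names the two factors but not the interaction.

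**Step 1: the plan's own figure.** For the interaction:
- df1 = (2 - 1)(3 - 1) = 2; df2 = (44 - 2)(3 - 1) = 84.
- Critical F(2, 84) at alpha 0.05 = 3.105, which matches the stated 3.10.
- Noncentrality = N × 3 × f² / (1 - rho). With f = 0.25 and rho = 0.5: 44 × 3 × 0.0625 / 0.5 = 16.5.
- Power = 95.6%, and 44 is the smallest even N that reaches 95%.

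The stated N and critical F are therefore those of one test at an unadjusted 5%. The pair f = 0.25, rho = 0.5 is not the only one that fits: f = 0.10 with rho = 0.92 gives 44 × 3 × 0.01 / 0.08 = 16.5 as well. Any pair with this noncentrality gives the same power.

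**Step 2: false-positive rate if any one significant result counts.** Under independence the rate is 1 - 0.95^k:
- k = 2: 1 - 0.95² = 9.75%.
- k = 4: 1 - 0.95⁴ = 18.5%.

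For correlated outcomes, k group-by-time F tests were simulated under no effect (N = 44, equal groups, 20,000 runs). Two-sided z tests (400,000 draws) served as a cross-check for k = 4.

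| r | k = 2, F tests | k = 4, F tests | k = 4, z tests |
|---|---|---|---|
| 0.3 | 9.6% | 16.9% | 17.4% |
| 0.5 | 9.2% | 15.9% | 15.6% |
| 0.7 | 8.3% | 13.6% | 13.0% |
| 0.8 | 7.5% | 11.7% | 11.4% |

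**Step 3: if every primary score must be significant.** The false-positive rate is at most 5%, since no joint success can be more likely than success on one true-null score. Power then falls: if the tests were independent, the chance that all succeed would be 0.956² = 91.4% for two and 0.956⁴ = 83.5% for four. Correlation raises this, but not above the single-test 95.6%.

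**Step 4: cost of adjusting.** The strictest Holm step for four scores is 0.05 / 4 = 0.0125. With the noncentrality from Step 1, power at N = 44 falls from 95.6% to 87.4%. With f = 0.25 and rho = 0.5, 56 completers would be needed for 95%. At 40% dropout, 70 recruits leave 70 × 0.6 = 42 completers, for whom the corresponding powers are 94.6% at 0.05 and 85.3% at 0.0125.

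**The case against.** The strongest reply is that this is a condensed article and that multiplicity control is commonly left to an analysis plan, which is not shown. That is fair: the absence of an adjustment here does not prove that none exists. What remains is what the article does fix: plural primary outcomes, a separate ANOVA for each measure, and a sample size built on one unadjusted test. A Holm or Bonferroni rule elsewhere would not fit that sizing, as Step 4 shows.

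A reader might infer something stronger: four or more primary tests, each at 5%, and hence a false-claim rate of 13-18% as a fact about this trial. The text does not support that, for four reasons.
- It fixes only two primary measures. Four is the natural reading, because only domain scores are described for the DASS, but separate domain tests are never stated.
- The 5% is stated for the sample-size calculation, not as a per-test level for the analysis.
- Any inflation requires that one significant result suffices. The hypothesis joins mental health and well-being with a conjunction and could mean that both are needed.
- The lower end of 13% requires a correlation near 0.7, which the article does not give.

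Nor is there a basis for counting the three aspects of the Mental Health Continuum as separate tests, since the article gives that instrument one total score.

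**Conclusion.** The concern holds in conditional form. As written, the plan does not keep the primary claim at 5% if any one significant primary score is taken as success. The rate is then about 7.5-10% for two scores and about 11-19% for four, over assumed between-outcome correlations of 0.8 down to 0. If all primary scores must be significant, the rate is at most 5%, but the stated 95% power no longer describes the primary objective. On either reading, the single-test sizing and the multi-test objective do not match, and the article does not say which reading applies. This affects how the main result may be read. It does not invalidate the trial, and it should be settled before the data are analysed.

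**What to change.** Before analysis, state which DASS scores are primary: the three domains, or one specified score. Apply Holm's procedure at a family-wise alpha of 5% to the planned group-by-time tests of the Mental Health Continuum total and those DASS scores. Treat the secondary scales as supportive. The adjustment belongs on the planned three-time-point tests, because the power figures above are for those and not for a posttest-only comparison.

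The change needs no new data or participants. Its cost is power: about 87% instead of about 95% at the strictest step for four scores with N = 44, under f = 0.25 and rho = 0.5, values worked back from the stated N and not given in the article. Later Holm steps are less strict, and with only two scores the strictest step is 0.05 / 2 = 0.025.

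Naming one score as the sole primary outcome would also restore the 5%, but it is not free. It would demote an outcome that the Objectives call primary, in a registered trial that had 30 + 34 = 64 of its 70 participants enrolled by October 2, 2019.

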### Assessments

The data collection methods were developed and refined for acceptability from a previous pilot [21]. All participants will complete measures before randomization and at equivalent time frames post intervention and follow-up. Posttest completion will be immediately after the 6-week intervention (approximately 6-8 weeks after the completion of the prequestionnaire), and the follow-up questionnaire will be completed 6 weeks after the posttest. Participants will be sent online survey links and reminders using the REDCap database.

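### The named repeated-measures ANOVA, in its classical form, keeps only participants with all three questionnaires, which conflicts with the promise to include everyone when up to 40% may drop out

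*Protocol article*

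**What the plan says.** The Data Analysis section of the protocol article names one quantitative method. Outcomes will be "examined at pre, post, and follow-up time periods using analyses of variance on each of the measures outlined above". The model is given next: "There will be a within-subjects factor (time) and a between-subjects factor (intervention/control"). The section then fixes the population: "Data analysis will employ the intention-to-treat principle by including all participants in the analyses". The Abstract repeats both the ANOVA and the intention-to-treat statement.

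The Participant Numbers section gives "a minimum of 44 participants, with Crit F=3.10", obtained by "assuming 2 groups and 3 repetitions, a small effect size, an alpha of 5%, and power of 95" per cent. It then says, on the basis of the pilot, that "there may be a dropout rate of up to 40" per cent, and concludes: "As a consequence, recruitment numbers were increased to 70".

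The Assessments section sets the waves: baseline before randomisation, a posttest about 6 to 8 weeks later, and "the follow-up questionnaire will be completed 6 weeks after the posttest". No section mentions imputation, a mixed model or any other way for a participant with a missing wave to enter the analysis.

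**The concern.** A classical repeated-measures ANOVA needs a score at every level of the within-subjects factor. Anyone missing the posttest or the follow-up is removed as a whole, including the scores that were collected. A participant who completes the posttest but not the follow-up contributes nothing, even to the posttest comparison. The population statement asks for the opposite.

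Two things are at stake. One is the label: a completer analysis could be reported as intention-to-treat. The other is validity: those with all three questionnaires are a group selected after randomisation. If the reasons for leaving are related to outcome and differ between a moderated website and a wait list, the comparison of completers is no longer protected by randomisation. Both primary outcomes, the Mental Health Continuum short form and the Depression, Anxiety, and Stress Scale, would be analysed this way.

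**Working it through.** **1. Inputs from the article.** Two groups, three waves, alpha 0.05, power 0.95, minimum N 44 and critical F 3.10, dropout up to 40%, recruitment 70 (Participant Numbers); time-by-group ANOVA and inclusion of all participants (Data Analysis). The correlation between waves and a numeric effect size are not given.

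**2. The plan's own figure.** For the time-by-group interaction with m = 3 waves and g = 2 groups:

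- noncentrality λ = N·f²·m/(1 − ρ); df1 = (m − 1)(g − 1) = 2; df2 = (N − g)(m − 1).
- With assumed ρ = 0.5, sphericity and f = 0.25, N = 44 gives λ = 44 × 0.0625 × 3/0.5 = 16.5, df2 = 84, critical F = 3.105 and power 0.956.

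So 44 and 3.10 reproduce, and they belong to an ANOVA in which each of the 44 has all three waves. (The value f = 0.25 is conventionally medium rather than small. That is a separate matter.)

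**3. Who is analysed at 40% dropout.**

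- Complete cases: 70 × 0.60 = 42.
- Randomised but excluded: 70 − 42 = 28.
- Power with 42 at f = 0.25, ρ = 0.5: 0.946, against 0.956 with 44.
- Recruitment needed to keep 44 at 40% loss: 44/0.60 = 73.3, so 74. Recruiting 70 covers loss up to 1 − 44/70 = 37.1%.

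The loss of power is trivial. The point is that 60% of those randomised is not all of them.

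**4. Possible bias, as an illustration.** All inputs here are assumptions, not taken from the article: true effect zero, unit SD, correlation 0.5 between every pair of waves, 15% random loss by the posttest in each arm, and total loss of 40% in each arm. Later loss is random in the control arm. In the intervention arm it is more likely with a worse (higher-distress) posttest score. The figures are large-sample differences between arms in change from baseline among completers; a negative value is a spurious benefit.

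| Log-odds of later loss per SD (intervention arm) | Completers, posttest | Completers, follow-up |
|---|---|---|
| 0 (random loss) | about 0 | about 0 |
| 0.5 | -0.07 SD | about 0 |
| 1.0 | about -0.12 to -0.13 SD | about 0 |
| 1.5 | -0.16 SD | about 0 |

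Using every observed posttest, the bias is below 0.01 SD in each row. The follow-up contrast escapes because the assumed correlations are equal: selection on the posttest score shifts baseline and follow-up by the same amount, and the shift cancels in the difference.

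For scale, with 21 completers per arm the change score has variance 2(1 − 0.5) = 1, so the standard error of the contrast is √(1/21 + 1/21) = 0.31 SD. The bias is about 0.2 to 0.5 of a standard error (0.07/0.31 and 0.16/0.31).

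**The case against.** The strongest reply is that the article's only explicit statement about the population is that everyone is included. An ANOVA on imputed data, or a time-by-group model fitted to all observed scores, would honour it, and the handling of missing data is often left to an analysis plan that is not shown. This stands in part. A reader might infer that the trial cannot deliver intention-to-treat, or that the claim would be untrue; the article does not support that, because it does not rule out imputation. The conflict nevertheless remains in the text: the method and the population are both stated, and the method as named does not produce the population.

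A reader might also infer from the increase from 44 to 70 that a completer analysis is intended. That does not follow. Inflating for dropout is routine under any analysis, since missing outcomes cost information in a mixed model as well.

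Finally, a reader might take attrition bias as established. It is not. Ignoring an optional website is different from not answering a questionnaire. The surveys go out by separate links with reminders (Assessments), the two arms are measured on similar schedules (Recruitment and Screening, Assessments), completing all questionnaires earns a voucher (Reimbursement), and controls are later offered the intervention (Allocation/Randomization). Against that, the arms do receive different things, and Participant Numbers itself points to a longer time frame for the wait-list controls. Differential loss is possible, not shown. In the illustration, moreover, dropout depends on an observed score, which favours observed-data methods by construction.

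**Conclusion.** The point holds as a conflict between the stated method and the stated population. Unless incomplete cases are modelled or imputed, the classical ANOVA would leave out up to 28 of 70 randomised participants. The figure of 28 rests on the article's upper limit of 40%; lower dropout excludes fewer.

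Attrition bias is a risk conditional on outcome-related dropout that differs by arm. The -0.07 to -0.16 SD range shows a possible order of size in the posttest change contrast under the assumed inputs. It is not an estimate for this trial, and with random loss it is zero.

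**What to change.** Replace the ANOVA in the Data Analysis section with a likelihood-based linear mixed model for repeated measures (time, group and time-by-group) fitted to all observed data from every randomised participant. Keep baseline in the outcome vector, so that people with only a baseline score also remain. Multiple imputation before the ANOVA, with results pooled over imputations, is an acceptable alternative. Either way, state in one sentence how participants with missing waves enter the analysis.

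Add one sensitivity analysis under missing-not-at-random assumptions. Report any completer ANOVA as secondary and label it as such.

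The cost is a change of wording and slightly more analysis work. No additional data or participants are needed.

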### Dissemination Strategy

The outcomes of the trial will be disseminated at conferences and in peer-reviewed journals. The general public, including young adults and other interested family members, mental health practitioners, and policy makers, will be notified of the study through public forums, government reports, policy statements, newsletters, and traditional and social media.

## Discussion

### Principal Findings

This paper describes the evaluation protocol for mi.spot, an online intervention for young adults aged 18-25 years whose parents have a mental illness and/or substance use concern. The intervention has a strong theoretical basis, which is lacking in most interventions in this area [35]. Given that 21% to 23% of all young people have a parent with a mental illness [2], such an initiative has the potential to make a substantial difference to the lives of many young people. The results of this study will add to the high-quality evidence base of electronic health interventions for this group of young people [36].

Notwithstanding its potential, the typical low rates of engagement in other online interventions for young people [37] are concerning. The flexible nature of the intervention in which participants can do some, all, or none of site features (and just *lurk*) may mitigate problems with engagement. Whether greater involvement equates to greater gains and relatedly determining how much engagement is sufficient to promote change are research questions that warrant further investigation.

As age-specific interventions increase young adults’ use of mental health services [38], interventions such as mi.spot may also promote the use of other, ongoing services for this group of young adults. Similarly, future investigations might investigate how online support could be integrated into face-to-face treatments and the types of referral pathways that are needed (both from and to mi.spot). Likewise, how an online intervention compares with similar face-to-face interventions [8] also remains to be investigated.

### Limitations

Participants report their own diagnoses and that of their parents, and these are not independently verified. The aims of the intervention are made clear from the outset, and thus, all participants (including those in the control group) will have some understanding of the nature of mi.spot that may encourage them to seek support elsewhere during the wait period and hence impact results [39]. Future considerations will need to investigate the cost effectiveness of the intervention and develop implementation guidelines to embed the intervention into routine care, which is important information for the long-term sustainable scale-up of effective public health interventions.

### Conclusions

The transition to adulthood can be a vulnerable period for young adults who have a parent with a mental illness or substance use concern. Given the issues related to stigma, access, and reach, online interventions hold great promise in engaging and intervening with this at-risk group. Support for the mi.spot trial will enhance the evidence base of a highly accessible intervention, which aims to prevent or reduce the adverse impact of young adults’ parents’ mental illness and/or substance use, for a large (approximately 21-23% of the population) high-risk group of young adults.

## Abbreviations

IPA: interpretative phenomenological analysis
mi.spot: mental illness; supportive, preventative, online, targeted
